## Abstract

**Introduction:**

In Sub-Saharan Africa, the rising rates of cerebrovascular and cardiovascular diseases (CBD/CVD) are intersecting with an ageing HIV-infected population. The widespread use of antiretroviral therapy (ART) may confer an additive risk and may not completely suppress the risk associated with HIV infection. High-quality prospective studies are needed to determine if HIV-infected patients in Africa are at increased risk of CBD/CVD and to identify factors associated with this risk. This study will test the hypothesis that immune activation and dysfunction, driven by HIV and reactivation of latent herpesvirus infections, lead to increased CBD/CVD risk in Malawian adults aged ≥35 years.

**Methods and analysis:**

We will conduct a single-centre, 36-month, prospective cohort study in 800 HIV-infected patients initiating ART and 190 HIV-uninfected controls in Blantyre, Malawi. Patients and controls will be recruited from government ART clinics and the community, respectively, and will be frequency-matched by 5-year age band and sex. At baseline and follow-up visits, we will measure carotid intima-media thickness and pulse wave velocity as surrogate markers of vasculopathy, and will be used to estimate CBD/CVD risk. Our primary exposures of interest are cytomegalovirus and varicella zoster reactivation, changes in HIV plasma viral load, and markers of systemic inflammation and endothelial function. Multivariable regression models will be developed to assess the study’s primary hypothesis. The occurrence of clinical CBD/CVD will be assessed as secondary study endpoints.

**Ethics and dissemination:**

The University of Malawi College of Medicine and Liverpool School of Tropical Medicine research ethics committees approved this work. Our goal is to understand the pathogenesis of CBD/CVD among HIV cohorts on ART, in Sub-Saharan Africa, and provide data to inform future interventional clinical trials. This study runs between May 2017 and August 2020. Results of the main trial will be submitted for publication in a peer-reviewed journal.

**Trial registration number:**

ISRCTN42862937.

Strengths and limitations of this studyThis is one of the first large-scale studies in Sub-Saharan Africa to explore the relationship between HIV infection, latent herpesviruses, inflammation, and cardiovascular and cerebrovascular diseases, immediately after starting antiretroviral therapy (ART).Clinical events and death will be comprehensively reviewed through an endpoint review committee using strict diagnostic criteria for events based on those used in the INSIGHT (International Network for Strategic Initiatives in Global HIV Trials) network or validated verbal autopsy for death with limited data.Because of the recent roll-out of ART in asymptomatic patients, there will be an absence of ART-naïve population, limiting our ability to explore the impact of ART.Approximately one-third of strokes will be asymptomatic and we anticipate not capturing some of these; however, multiple cerebral infarcts without a focal neurological deficit will manifest as cognitive impairment, which we will screen for and corroborate with MRI in a small number of symptomatic cases.Two-thirds of myocardial infarction will be silent and could potentially be missed, and in a nested group we will use digital ECG to evaluate this further.

## Introduction

The growing epidemic of cerebrovascular disease (CBD; eg, stroke) and cardiovascular disease (CVD; eg, myocardial infarction (MI)) now intersects with the HIV epidemic.^1^ Countries such as Malawi have an adult HIV prevalence of approximately 10%.^2^ There is an increased life expectancy among people living with HIV, largely because of the successful scale-up of antiretroviral therapy (ART).^3^ In Europe and the USA, HIV is associated with a 50% increased risk of CVD compared with HIV-uninfected populations,^4^ attributable to long-term ART use and HIV per se.^4 5^ HIV infection is also associated with a 1.8-fold increased risk of all-cause heart failure in US veterans.^6^ Our recent case–control study of stroke in Malawian adults is one of several examples that demonstrate a high risk of HIV infection associated with stroke and heart disease, pointing to a considerable and unappreciated CBD/CVD risk among patients with HIV in this setting.^7–10^

There are reports of geographical differences in the distribution of CVD risk factors, supporting the argument that evidence derived from high-income countries cannot be applied to Sub-Saharan (SSA).^11^ Addressing this knowledge gap is essential to the development of clinical drug trials for primary prevention of CBD/CVD among individuals living with HIV. Vasculopathy due to accelerated atherosclerosis, arterial stiffening and vasculitis are the major mechanisms believed to underlie the CBD/CVD burden.^12 13^ It is hypothesised that despite viral suppression, low-grade HIV virus replication and the associated host systemic inflammation are important drivers of this vasculopathy (figure 1). In patients receiving ART, HIV antigenaemia, partly resulting from HIV persistence in sanctuary sites, incomplete virological suppression and virological resurgence, drives the chronic immune activation observed in about 20% of ART patients in SSA.^14^ This immune state is characterised by ongoing activation and senescence of cell-mediated immunity,^15 16^ increased monocyte/macrophage activation, stimulation of the interleukin-6 (IL-6) pathway and production of acute phase proteins.^17–19^ Activation of the IL-6 pathway is established with atherosclerosis^20 21^ and may also contribute to non-atherosclerotic vasculopathy. Inflammation alone confers a two-fold increased risk of clinical CBD/CVD events.^22^ The current push to introduce more effective ART regimens and to start treatment soon after HIV diagnosis is made may reduce inflammation and in turn CBD/CVD risk.^23^ However, there is growing evidence of chronic inflammation in HIV despite achieving the goal of therapy, which is long-term suppression (<50 copies/mL) of plasma viral load, suggesting adjunctive therapy may be required.^24–26^

**Figure 1 F1:**
[figure not shown]
Hypothetical pathway of the interplay between chronic viruses, immune activation, systemic inflammation, endothelial activation and vasculopathy. CIMT, carotid intima-media thickness; IL-6, interleukin-6; PWV, pulse wave velocity; VL, Viral Load; HLA-DR, Human Leukocyte Antigen-DR isotype; IFNγ, interferon gamma; TFNα, Tumour Necrosis Factor alpha; ICAM-1, intercellular adhesion molecules-1 and hsCRP, high-sensitivity C-reactive protein.

In addition to HIV, there is compelling evidence that reactivation of latent herpesviruses may be an important cause of vasculopathy. In HIV-uninfected elderly populations from high-income settings, latent cytomegalovirus (CMV) infection drives dysregulation of cell-mediated immunity,^15 27–29^ not dissimilar to what is described in HIV-associated immune activation.^29^ CMV and other viral proteins have been found in atherosclerotic plaques.^20^ Varicella zoster virus (VZV) can directly infect the vascular endothelium to cause vasculitis and subsequent stroke and was found to be the most common opportunistic infection (prevalence 15%) in a study of HIV-infected patients with stroke in Malawi.^12^ The seroprevalence of herpesviruses is high in SSA,^30^ particularly in HIV-infected populations.^16^

The involvement of herpesviruses in the mechanistic pathway for CBD/CVD is compelling and may offer additional therapeutic avenues, especially for CMV and VZV. However, our understanding is incomplete, and its population impact is yet to be defined. It is important to determine if, in addition to ART, there is a role for other pharmacological interventions targeting latent viral infections or downstream inflammatory pathways to reduce vasculopathy in HIV-infected patients on ART. Previous work from North America supports the potential of treating reactivated herpesviruses.^31^ Furthermore, there are opportunities for intervention using the recently licensed letermovir, a treatment for CMV. By focusing on HIV and herpes viral antigenaemia and immune dysregulation as mechanisms of vasculopathy, this study will identify subgroups of HIV-infected patients on ART at high risk of CBD/CVD, the timing of CBD/CVD risk in such patients, as well as potential targets for intervention. Utimately, the study goal is to investigate whether reactivation of herpesviruses and inflammation are cardiovascular and cerebrovascular risk factors in antiretroviral therapy initiators in an African HIV-infected population (RHICCA).

### Study objectives

This study will test the hypothesis that immune activation and dysfunction, driven by HIV and reactivation of latent CMV/VZV herpesvirus infections, lead to increased CBD/CVD risk in adults aged ≥35 years in SSA. We will address this through the following objectives:

To determine if progression of the surrogate marker of CBD/CVD or occurrence of new-onset vasculopathy is higher in adults aged ≥35 years with HIV infection on ART compared with those without HIV.To determine if progression of surrogate markers of CBD/CVD or occurrence of new-onset vasculopathy is higher in adults aged ≥35 years with HIV/herpes viral antigenaemia or chronic immune activation compared with those without HIV/herpes viral antigenaemia or chronic immune activation. Specifically, we will determine if progression of surrogate markers or new-onset vasculopathy is higher in the following:In ART patients with reactivated latent herpes viral infection, compared with those without reactivated latent herpes viral infection.In ART patients with the highest 25% of markers for immune activation, inflammation or endothelial activation compared with the bottom 25%.In ART patients with incomplete virological suppression or virological resurgence of HIV, compared with those with suppressed HIV plasma viral load.

The secondary study objectives are to determine if viral antigenaemia or chronic immune activation increases the occurrence of the following clinical events: (1) stroke, (2) MI, (3) angina (excluding MI), (4) peripheral vascular disease (PVD), (5) all-cause death/vascular-related death and (6) immune reconstitution inflammatory vasculopathy.

## Methods and analysis

### Study design

To address objective 1, we will conduct a single-centre, 36-month, prospective cohort study in 800 HIV-infected patients initiating ART and 190 HIV-uninfected adults aged ≥35 years. HIV-infected and HIV-uninfected participants will be frequency-matched by 5-year age band and sex. On a 6-monthly basis, we will measure markers of viral infection, inflammation and endothelial function along with surrogate markers for CBD/CVD (table 1).

**Table 1 T1:** Laboratory tests and clinical procedures in ART patients and HIV-uninfected adults

	Study time points						
	Baseline	6 months	12 months	18 months	24 months	30 months	36 months
Clinical procedures							
PWV	X	X	X	X	X	X	X
CIMT	X				X		
ABPI	X	X	X	X	X	X	X
Cardiac echo (participant subset)	X				X		
ECG (participant subset)	X				X		
Cardiometabolic markers							
Creatinine Full blood count	X X	X			X		
Cholesterol (LDL, HDL, triglycerides)	X				X		
Serum glucose/haemoglobin A1c	X				X		
HIV infection and progression							
HIV viral load (patients with HIV)	X	X	X				
CD4 count (patients with HIV)	X	X	X				
HIV rapid test (controls)	X		X		X		X
Immune dysregulation							
Soluble markers of systemic inflammation	X	X	X				
Soluble markers of endothelial activation	X	X	X				
CD8 and CD4 T cell activation and senescence (participant subset)	X	X	X		X		X
Monocyte/Macrophage activation and senescence (participant subset)	X	X	X		X		X
Herpesviruses infection							
CMV IgG	X	X					
VZV IgG	X	X					

ABPI, Ankle Brachial Pressure Index; ART, antiretroviral therapy; CIMT, carotid intima-media thickness; CMV, cytomegalovirus; HDL, high-density lipoprotein; LDL, low-density lipoprotein; PWV, pulse wave velocity; VZV, varicella zoster virus.

### Study setting

This study will recruit consecutive ART patients from the ART clinic of Queen Elizabeth Central Hospital (QECH) and ART clinics in several Blantyre City community health centres (CHCs). These clinics collectively initiate over 100 HIV-infected patients aged ≥35 years onto ART each month. HIV-uninfected adults will be selected from pre-ART counselling sessions, and from randomly selected households in the community by two-stage random sampling (of households and individuals within households) from a previously enumerated sampling frame in the CHC catchment areas.^32^ All study procedures will be conducted at the QECH, which is located adjacent to the Malawi-Liverpool-Wellcome Trust Clinical Research Programme (MLW). The QECH also hosts a 0.35T MRI facility, which will contribute to characterising our secondary endpoints.

### Study participants

Study inclusion criteria will be (1) age ≥35 years and (2) resident of Blantyre. HIV-infected patients must further be (3) ART-naïve or initiated ART <10 days prior to enrolment and (4) initiating standard first-line ART. Adult controls must further be (5) HIV-uninfected. Study exclusion criteria are (6) clinical history of CBD/CVD, (7) pregnancy, (8) critical illness or symptomatic anaemia at baseline, and (9) enrolment in an intervention study. At the analysis stage abnormal pulse wave velocity (PWV) at baseline (as defined in table 2) will be excluded for new-onset vasculopathy analysis but not for progression of vasculopathy. The same approach will be applied for baseline carotid intima-media thickness (CIMT) measurements. If the study participant becomes pregnant after recruitment, they will be withdrawn.

**Table 2 T2:** Case definitions of primary and secondary endpoints for the study

Type	Definitions
Primary endpoint	Carotid intima-media thickness (CIMT)	*The occurrence of new-onset vasculopathy**(**CIMT, a measure of atherosclerosis**)*: CIMT >0.9 mm or >75th percentile of age/sex references values or presence of plaque on the carotid scan. *Progression*: total change in CIMT at 24 months from baseline.
	Pulse wave velocity (PWV)	*Occurrence of new-onset vasculopathy**(**PWV*,*a measure of arterial stiffness**)*: PWV >12 (m/s). *Progression*: total change in PWV at 24 months from baseline.
Secondary endpoint	Stroke	*Confirmed (**1**+**2**) or 3 or 4 or 5:* Acute onset with a clinically compatible course, including unequivocal objective findings of a localising neurological deficit. CT or MRI compatible with a diagnosis of stroke and current neurological signs and symptoms. Stroke diagnosed as the cause of death at autopsy. Clinical history and positive lumbar puncture compatible with subarachnoid haemorrhage. Death certificate or death note from medical record listing stroke as the cause of death.
	Myocardial infarction (MI	*Confirmed:**o**ne of the following**five**criteria (adapted from**2007**Universal Definition of**Myocardial Infarction**)**(**1 + (2 or 3**or 6))**or 4 or 5*: Rise and/or fall of cardiac biomarkers (preferably troponin), with at least one value above the 99th percentile of the upper reference limit. The occurrence of a compatible clinical syndrome, including symptoms consistent with myocardial ischaemia. ECG changes indicative of new ischaemia (new ST changes or new left bundle branch block (LBBB)), or development of pathological Q waves on the ECG. Sudden unexpected cardiac death involving cardiac arrest before biomarkers are obtained or before a time when biomarkers appear, along with (a) new ST changes or new LBBB, or (b) evidence of fresh thrombus on coronary angiography or at autopsy. Pathological findings of acute MI (including acute MI demonstrated as the cause of death on autopsy). Development of (a) evolving new Q waves or (b) evolving ST elevation, preferably based on at least 2 ECGs taken during the same hospital admission.
	Coronary artery disease requiring drug treatment	*Confirmed (**1**or 2)**+**3*: Evidence of myocardial ischaemia based on either diagnostic imaging (such as a stress echocardiogram or thallium scan) or diagnostic changes on an ECG (such as during stress testing or an episode of chest pain). Evidence of coronary artery disease based on coronary angiography or other diagnostic imaging. Use of medication given to treat or prevent angina (eg, nitrates, beta blockers, calcium channel blockers).
	Peripheral vascular disease	*Confirmed (**1**+**2**) or (**1**+**3**)*: Compatible clinical signs and symptoms. Positive results on diagnostic imaging studies (eg, Doppler ultrasound, contrast arteriography, MRI arteriography). Ankle brachial pressure index <0.90 in non-diabetics.
	Vascular Immune reconstitutionsyndrome (IRIS)	A new onset vasculopathy within 6 months of starting ART
	All-cause death and vascular-related deaths	Death (of any or vascular cause) that occurs after recruitment into the study.

Justification of study inclusion and exclusion criteria is as follows: in many populations, CBD/CVD risk rises sharply from 35 years of age^33^; thus, individuals aged 35 and older will be eligible (recruitment of participants aged 35–39 will be limited to 15% of the study sample to avoid over-representation). Restricting recruitment by age will enable this study to have greater statistical power. For clarity of aetiological inference, the study will assess the risk of new-onset vasculopathy not associated with pregnancy and thus exclude patients who are pregnant or with a history of CBD/CVD. To eliminate confounding by ART regimen, patients must initiate on standard first-line ART (>90% of ART patients in Blantyre do this). Critically ill patients are excluded primarily for ethical reasons.

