### Secondary outcomes

The secondary outcomes are the following clinical events: (1) stroke, (2) MI, (3) unstable angina, (4) PVD, (5) all-cause death/vascular death and (6) immune reconstitution inflammatory syndrome (IRIS) vasculopathy (table 2). Changes in PWV or endothelial activation at 6 months post-ART initiation will be interpreted as a subclinical vascular IRIS event. These outcomes will be assessed through active surveillance in QECH inpatient wards for admissions of study participants. To improve capture of clinical outcomes, we will conduct brief telephone interviews with study participants about CBD/CVD symptoms and hospitalisations between study visits and facilitate unsolicited participant self-report. Clinical events and deaths in study participants will be reviewed by an independent endpoint review committee (ERC), comprising clinicians experienced in endpoint review. Each event will be reviewed and adjudicated by the ERC chair and two ERC reviewers, using a standard set of diagnostic criteria (table 2 and online supplementary S1). The format of reporting will be based on modifications of the INSIGHT network clinical diagnostic criteria. Deaths will be reviewed by the ERC using the International Classification of Diseases for causes of death classificaton.^23^ For death with limited clinical data, a validated verbal autopsy will be performed to ascertain the cause.^38^

10.1136/bmjopen-2018-025576.supp1Supplementary data

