### Exposures

The exposure for primary objective 1 will be HIV status. Yearly HIV rapid tests in HIV-uninfected adults will be performed to exclude those with new HIV infections (figure 2).

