### Data collection between May 2017 and August 2020

The two-stage screening will be conducted to find and recruit potential study participants. A trained fieldworker will first screen to assess eligibility for criteria 1–3 in pre-ART counselling sessions and in individuals from randomly selected households in the community. Eligible participants will then be referred to the QECH to complete screening for criteria 4–9, and if eligible consented to participate in the study. At study visits, a tablet-based, standardised Open Data Kit case report form will be administered in one-on-one interviews by a study nurse to capture demographic and clinical data. Study data will be collected as outlined in table 1. Daily upload of electronic data will occur with oversight from the data manager at MLW. We will collect up to 30 mL of whole blood. Urine albumin to Creatinine ratio (ACR) dipstick test will be used to test for creatinine, proteinuria and glucosuria. In a subset of participants, an ECG supported by a digital platform and echocardiogram will be performed at baseline and at 6 and 24 months, as well as in any participant experiencing a clinical event suggestive of a cardiac aetiology. To facilitate the retention and clinical referrals of participants, contact will be made every 3 months to assess the occurrence of clinical events. Participants who miss a scheduled study visit will be contacted by phone and/or visited at home to assess their willingness to maintain their participation and to record intervening clinical events. Recording and definitions of other clinical events, including HIV-associated events, will be evaluated by the ERC chair. SMS (short message service) messages will be used for appointment reminders. A technical appendix, statistical code and study data sets will be made available from a data repository, after publication of our work.

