### Sample size and statistical analysis

The required sample size for the study’s primary objectives is 800 HIV-infected patients and 190 HIV-uninfected adults using standard, normal distribution approximation sample size formulas for comparing proportions in two groups of unequal size and based on the following assumptions: (1) of HIV-infected study participants, 18.4% have abnormal PWV at baseline. We will exclude these participants from analysis. The 18.4% figure is informed by our ongoing studies of vasculopathy in HIV-infected patients, where this is the percentage of participants aged ≥35 years who have a PWV (>12 m/s). (2) Of both HIV-infected patients and HIV-uninfected adults, 20% will be lost to follow-up, including by death and HIV seroconversion.^40 41^ (3) The minimum relative risk (RR) of interest is 2 for objective 1 and 1.8 for objective 2. (4) The 24-month cumulative risk of clinically significant vasculopathy over study follow-up is 18.4% in the HIV-positive group. This is based on the same study data cited in (1). (5) For objectives 2a–2c, the exposure prevalence for each risk factor is 20%. (6) Statistical tests will have 80% power based on a two-sided test with α=0.05. Testing of hypotheses for the secondary outcome will be exploratory. However, we estimate 26 strokes (4 mimics), an unknown number of MIs and 80 deaths occurring during the study.^7 42^ Taken together, assumptions (3), (4) and (5) mean that, for 80% power, we assume a 24-month cumulative vasculopathy risk of 9.2% in HIV-negative participants, 18.4% in all HIV-infected participants, 15.9% in HIV-infected participants not exposed to the risk factors from objectives 2a–2c and 28.6% in the HIV-infected participants exposed to these risk factors.

The reporting of this study will be prepared in accordance with the Strengthening the Reporting of Observational Studies in Epidemiology guidelines.^43^ Summary and descriptive statistics will be tabulated for all primary and secondary outcome variables, as well as for exposure variables and potential confounding or mediating factors. Time plots for all outcome variables will be inspected. Quantitative data analysis will be conducted to assess the primary outcomes.

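### Participants who become pregnant are withdrawn outright, with no provision to follow them for death or clinical events; the likely loss is small but selective and avoidable.

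*Protocol article*

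**What the plan says.** All references are to the protocol article.

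- **Study participants.** Pregnancy is a baseline exclusion. The text then adds: "If the study participant becomes pregnant after recruitment, they will be withdrawn". No exception is made for clinical events or vital status.
- **Study participants, justification of criteria.** The reason given is that "the study will assess the risk of new-onset vasculopathy not associated with pregnancy and thus exclude patients who are pregnant", and likewise those with a history of CBD/CVD.
- **Table 2.** New-onset vasculopathy is defined by CIMT (with plaque) and PWV thresholds. The death endpoint is "Death (of any or vascular cause) that occurs after recruitment into the study".
- **Secondary outcomes.** Events are found through "active surveillance in QECH inpatient wards for admissions of study participants", together with telephone interviews and self-report.
- **Data collection.** Contact is made every 3 months. Tracing is described for missed visits: "Participants who miss a scheduled study visit will be contacted by phone and/or visited at home".
- **Table 1.** CIMT is measured at baseline and 24 months only; PWV and ABPI are measured every 6 months.
- **Sample size and statistical analysis.** Cox models are planned for all-cause mortality, and Poisson or negative binomial models for clinical events if there are enough of them. Primary analyses use multiple imputation.

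**The concern.** A condition for entry has become a reason to end observation after entry. The study gives no treatment, so the rule protects no participant from a study intervention, and its stated purpose is aetiological. That purpose is met by not using vascular measurements that pregnancy may have altered. It does not require that later deaths, later strokes or a scan after delivery go unrecorded.

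Three things are at stake:

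- **Endpoint definition.** A woman withdrawn at pregnancy who later dies meets the Table 2 definition of death, but nothing in the article provides for observing that death.
- **Selective censoring.** Follow-up ends at a post-baseline event confined to women of childbearing potential, so the censoring in the mortality and event models is selective by sex and age.
- **Avoidable imputation.** CIMT progression rests on two scans. Withdrawal before month 24 removes the second, and imputation replaces a value that could have been measured once pregnancy had ended. Imputation and mixed models do nothing for unobserved deaths or strokes.

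**Working it through.** **1. Rule against reason and endpoints.** The rule removes the person. The reason concerns one outcome, which Table 2 defines by PWV and CIMT. All-cause death, and clinical events well after delivery, fall outside that reason but inside the endpoints. The same section treats abnormal baseline PWV more narrowly: those participants stay in the study and are left out of the new-onset analysis only.

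**2. The plan's own sample size.** Inputs: 800 HIV-infected and 190 uninfected; 18.4% of the HIV-infected excluded for abnormal baseline PWV; 20% loss; two-sided α = 0.05. The method is the normal approximation with pooled variance under the null and no continuity correction.

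- Evaluable HIV-infected: 800 × 0.816 × 0.8 = 522.
- Evaluable controls: 190 × 0.8 = 152 (no baseline PWV exclusion applied to controls).
- Power = Φ[(|p1 − p2| − 1.96·SE0)/SE1], where SE0 uses the pooled risk and SE1 the separate risks.
- Objective 1 (9.2% v 18.4%): SE0 = 0.03406 and SE1 = 0.02893, so (0.092 − 1.96 × 0.03406)/0.02893 = 0.87 and power is 80.8%. The formula asks for 150 evaluable controls, or 150/0.8 = 188 recruited, against the stated 190.
- Objective 2 (28.6% v 15.9%, split 1:4): 495 evaluable needed, or 495/(0.8 × 0.816) = 758 recruited. The stated 800 gives 82.1%.

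The stated sample size therefore reproduces closely.

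**3. How many might be withdrawn.** The documents give no pregnancy rate, sex split or age distribution, apart from the 15% cap on ages 35–39. Everything else here is assumed: 55–65% women; 15% of women aged 35–39 (the cap, spread evenly by sex); 15–25% of women aged 40–44; 3–8 pregnancies per 100 woman-years at 35–39 and 1–4 at 40–44; 24 months.

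- Low: 990 × 0.55 × (0.15 × 0.03 × 2 + 0.15 × 0.01 × 2) = 544.5 × 0.012 = 6.5, about 7 (0.7%).
- High: 990 × 0.65 × (0.15 × 0.08 × 2 + 0.25 × 0.04 × 2) = 643.5 × 0.044 = 28.3, about 28 (2.9%).

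**4. Events missed.** The plan expects 80 deaths and 26 strokes. If events are spread evenly over participants and every event in a withdrawn woman falls after withdrawal (an upper bound under even spread):

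- Deaths: 80 × 0.0066 = 0.5 to 80 × 0.0286 = 2.3.
- Strokes: 26 × 0.0066 = 0.2 to 26 × 0.0286 = 0.7.

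**5. Power.** If these losses come on top of the 20%, both groups shrink by the same fraction:

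| Extra loss | Objective 1 | Objective 2 |
|---|---|---|
| 0 | 80.8% | 82.1% |
| 0.66% | 80.6% | 81.9% |
| 2.86% | 79.6% | 81.1% |
| 5% (beyond the assumed range) | 78.6% | 80.3% |

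If the 20% allowance already covers pregnancy, power does not change.

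**The case against.** The strongest reply is that the article does not say what withdrawal covers. Ward surveillance does not depend on study visits, and a full protocol may keep vital status for withdrawn participants. This stands in part: the loss of events is inferred from the word withdrawn. But the rule is stated without qualification, surveillance is described for study participants, and tracing is described for missed visits. Followed as written, the rule ends observation.

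It can also be said that the reason is wider than PWV and CIMT. It is offered for clarity of aetiological inference, and a stroke during pregnancy may itself be pregnancy-related. This stands for vascular events during pregnancy, which is why they should be flagged. It does not reach all-cause death or events after pregnancy.

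Third, the consequence is small. The affected women are the youngest in the cohort, testing of secondary outcomes is exploratory, age and sex can be conditioned on, and mixed models use PWV recorded before withdrawal. All of this stands.

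A reader might infer more than the documents support:

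- **That the 20% allowance leaves pregnancy out.** The text reads "20% will be lost to follow-up, including by death and HIV seroconversion"; a list introduced by including is not exhaustive.
- **That data from controls who seroconvert are discarded.** The Exposures section says "Yearly HIV rapid tests in HIV-uninfected adults will be performed to exclude those with new HIV infections", but does not say that earlier data are dropped, and counting seroconversion under loss to follow-up fits keeping them.
- **That the loss depends on health or HIV status.** The documents give nothing on this.
- **That some 50 participants would be lost.** Such a figure needs half of the women to be aged 35–44, all conceiving at the highest rate assumed for ages 35–39, and takes no account of the 15% cap.

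**Conclusion.** The point holds as a modest design fault. The withdrawal rule goes further than its stated reason, sits badly with a death endpoint that counts any death after recruitment, and gives up follow-up CIMT that could often be obtained. The case rests on avoidable, selective loss of endpoint data, not on power, and no figure in the sample size section is wrong on this account.

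The size, about 7 to 28 of 990 participants over 24 months, rests wholly on assumed rates apart from the 15% cap. Some participants will be followed for up to 36 months; at constant rates over that whole period the counts would be 1.5 times larger (about 10 to 42), which is still a small share of the cohort. The conclusion also assumes that withdrawal means the end of event follow-up. If the full protocol already retains it, the remaining change is to say so.

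**What to change.** Replace the withdrawal sentence under Study participants with wording to this effect: participants who become pregnant remain in follow-up, with their consent, for clinical events and vital status through the existing 3-monthly contacts and ward surveillance; PWV, CIMT and ABPI values taken during pregnancy, or in a pre-specified window after it, are left out of the vasculopathy analyses; measurements before and after that period are kept, including the 24-month CIMT where it falls outside the window.

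Add that vascular events occurring during pregnancy are flagged, and that a sensitivity analysis of the clinical-event models is run without them.

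The cost is a protocol amendment, consent wording and a pregnancy flag in the data; the contacts already exist. The downside is gaps in a few PWV series, which the planned mixed models handle. Where the 24-month CIMT falls inside the window it remains missing, and is imputed as now planned.
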